### Baseline patient characteristics

The study anticipates summarizing a number of baseline participant characteristics at the individual, household, and cluster levels. Table 6 lists these minimum baseline participant characteristics and the expected summary measures which will be summarized in the cohort and cross-sectional surveys.

**Table 6 Tab6:** Baseline patient characteristics

Characteristic	Cohort summary measure	Cross-sectional summary measure
**Cluster level**		
** Number of clusters**	*N*	*N*
** Cluster size**	Mean *N* HH (total HH)	Mean *N* HH (total HH)
** Cluster size**	Mean *N* residents (total *N*)	Mean *N* residents (total *N*)
** Cluster size (sampling areas)**	Mean *N* residents (total *N*)	Mean *N* residents (total *N*)
** Cluster size (buffer zones)**	Mean *N* residents (total *N*)	Mean *N* residents (total *N*)
** Baseline incidence**	Mean Incidence rate of clinical malaria in baseline cohort per person month (variance)	Mean incidence rate of clinical malaria in baseline cohort per person month (variance)
** Baseline prevalence**		Proportion positive by RDT for *P. falciparum* at baseline
**Household level**		
** HH size**	Mean *N* residents (SD)	Mean *N* residents (SD)
** LLIN ownership**	Proportion HH with ≥ 1 LLIN (first interview)	Proportion HH with ≥ 1 LLIN
** LLIN ownership**	Proportion HH with ≥ 1 LLIN per 2 residents (first interview)	Proportion HH with ≥ 1 LLIN per 2 residents
**Individual characteristics**		
** Age**	Mean age (SD)	Proportion under five
** Sex**	Proportion female	Proportion female
** HH size**	Mean hh size of participant’s HH (SD)	Mean hh size of included hh (SD)
** Net use**	Proportion slept under the net night before the survey	Proportion (tested population) slept under the net night before the survey

## Analysis

### Outcome definitions

The primary outcome measure is the incidence rate of clinical malaria cases assessed among people aged 12 months to less than 15 years (≥ 5 to 15 in Mali). A clinical case is defined as having an axillary temperature of ≥ 37.5 °C or self-reported fever within the past 48 h, plus a positive malaria RDT. Incidence rate is defined as the total number of incident malaria cases divided by the total person-time observed among each cohort. Outcome assessment will be conducted on each cohort participant monthly. As malaria treatment drugs will be administered to all positive clinical cases (fever + positive RDT) after monthly case ascertainment, each positive (treated) participant will have 2 weeks of the following month of observation time subtracted from their at-risk person-time to account for the prophylactic effect due to sustained antimalarial drug concentration and hence not being at risk of infection. In individuals who are symptomatic and have a positive RDT test in the month following a positive diagnosis of malaria via RDT and treatment, a positive RDT in the following month may indicate persistence of antigen in the blood after effective treatment rather than true reinfection. In such cases, PCR or microscopy results for a *Plasmodium falciparum* infection will be used to resolve if the positive RDT is a result of persistent antigenemia or a true infection (reinfection/recrudescence). In Mali, only microscopy will be used to resolve such cases. In Kenya and Zambia, PCR results will be used where available, and otherwise microscopy. Where the RDT and either the PCR or microscopy results are both positive in month two and the patient meets the other clinical criteria (patent fever or history of fever in the previous 48 h), these observations will be treated as new clinical cases. To keep field procedures unambiguous, a blood slide will be taken whenever a positive RDT is recorded in Mali. Temporary absences from the study area not resulting in failure to ascertain monthly outcomes will not be considered as reducing individual exposure time. Absences greater than the testing interval (1 month ± 5 days) and/or resulting in the failure to ascertain a monthly test result will be removed from the exposure time—meaning that exposure will only be considered to start 1 month prior to the most recent test result.

In summary:If a participant is symptomatic and positive by RDT, they are treated and the subsequent 2 weeks of follow-up time are censored.If in the next month the participant is also symptomatic and again positive by RDT, they will be treated and PCR or microscopy will be used to determine if they are considered a case of persistent antigenemia or a true new clinical caseIf PCR or microscopy in month two is positive, they are considered to have contributed the person-time between the previous visit and this visit less than 2 weeks and they are considered to contribute a second case to the numerator; two more weeks of follow-up will be censored following the second positive. In Mali, a person who is a malaria case on the day they re-enter the study does not contribute to the number of cases as no follow-up is associated with the case, i.e., they contribute neither to the numerator nor the denominator until they have contributed follow-up.If PCR or microscopy is negative, then contributed follow-up time between the previous visit and the second visit with the second positive RDT is included (minus 2 weeks) and only one case is included in the numerator; however, two more weeks of follow-up time are censored after the second RDT positive (due to the required treatment).

### Secondary outcomes

1. RDT infection prevalence

Prevalence of patent malaria infection detected by RDT among participants aged 6 months and older is calculated as the number of eligible, consenting participants with positive RDT results divided by the number of eligible, consenting participants with valid RDT results, collected during the cross-sectional survey (rolling survey in Kenya).2. Passive incidence

Incidence rate of passively reported clinical malaria among participants of all ages, defined as the number of malaria confirmed cases (by RDT or microscopy), linked to study clusters by place of residence, per 1000 population per year, using routine data from health facilities with patients linked to study clusters (i.e., by name of the village of residence) and cluster population sizes for the denominator. Cluster population sizes will be calculated based on the number of HH residents identified in the cluster area (core only where possible/relevant) during the census/enumeration. Malaria-confirmed cases will include only those given a diagnosis of blood test (RDT or microscopy) confirmed malaria (ICD-10-M B50-54 and subcodes).3. Parity

The parity outcome is the non-parous proportion: the proportion of freshly caught, non-blood-fed female adult *Anopheles* spp. mosquitoes captured during human landing catch which have never been gravid (are parous) as determined by the method of Detinova (1962). The outcome is assessed in a sub-sample of clusters, houses, and nights. Data will be disaggregated by species (and/or sub-species) with species determination made by taxonomic key and PCR where necessary. Mosquitoes will be classified as parous or non-parous. Mosquitoes with inconclusive results will be excluded from the analysis of parity.4. Mosquito abundance

The number of adult *Anopheles* spp*.* captured in CDC UV light traps per night per trap. The outcome is assessed in a sub-sample of clusters, houses, and nights. Data will be disaggregated by species (and/or sub-species) with species determination made by taxonomic key and PCR where necessary. Mosquitoes with inconclusive speciation will be included in total *Anopheles* spp. abundance calculations but excluded from any species-specific analyses.5. Sporozoite rate

The number of adult female *Anopheles* spp. captured via HLC or CDC UV light trap found to be sporozoite positive by anti-circumsporozoite protein (α-CSP) enzyme-linked immune-sorbent assay (ELISA) divided by the number of adult female *Anopheles* spp*.* tested in ELISA assay. The outcome is assessed in a sub-sample of clusters, houses, and nights. Data will be disaggregated by species (and/or sub-species) with species determination made by taxonomic key and PCR where necessary. Mosquitoes with inconclusive speciation will be included in total *Anopheles* spp. sporozoite rate calculations but excluded from any species-specific analyses. Mosquitoes with inconclusive α-CSP ELISA results will be excluded from all calculations.6. Human landing/biting rate

The number of adult female *Anopheles* spp. captured via HLC divided by the number of person-nights (days) of HLC collection. The outcome is assessed in a sub-sample of clusters, houses and nights. Data will be disaggregated by species (and/or sub-species) with species determination made by taxonomic key and PCR where necessary. Mosquitoes with inconclusive speciation will be included in total *Anopheles* spp. landing rate calculations but excluded from any species-specific analyses. Data will also be disaggregated by indoor versus outdoor collection location.7. EIR

For each month, the month-specific human landing/biting rate will be multiplied (6) by the month-specific sporozoite rate (5) to yield month-specific EIRs. Month-specific EIRs will be summed over the months of the year to yield the number of infectious bites expected in each year. This is a calculated outcome and will be disaggregated by species (and/or sub-species). Results will always be presented in terms of annualized EIR (e.g., number of expected infectious bites per person per year) even when the EIR estimate is made for specific months or other periods.

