^a^Prevalence estimates are for individuals aged ≥ 1 month (Kenya only)

^b^Per year in Kenya as trial uses a continuous survey approach

**Table 4 Tab4:** Sample size and power characteristics of each trial for entomological measures

	**Kenya**	**Zambia**	**Mali**
Clusters per arm	8 (16 total)	10 (20 total)	15 (30 total)
α	0.05 (two-tailed)	0.05 (two-tailed)	0.05 (two-tailed)
β	0.20 (> 80% power)	0.20 (> 80% power)	0.20 (> 80% power)
Number of months of sampling per cluster	12	8	24
Number of sampling sites (households) per cluster per month	10	10	10

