#### Secondary outcomes

Prevalence of malaria infection among participants aged 6 months and older, detected by RDT. This outcome will be assessed annually cross-sectionally (or through a rolling prevalence survey in Kenya). For the cross-sectional analyses (Zambia, Mali), measurement will occur in each member of the study sample within an approximate 1-month (30-day) observation window.Incidence rate of passively reported clinical malaria among participants of all ages, defined as the number of malaria confirmed cases (by RDT or microscopy), linked to study clusters by place of residence, per 1000 population per year, using routine data from health facilities serving the study population (e.g., by name of village of residence) and cluster population sizes for the denominator. This outcome is assessed daily at routine health facilities and dispensaries (Mali and Kenya only).Parity as a proxy for daily female vector mosquito survival—this outcome is defined as the non-parous proportion, e.g., the proportion of freshly-caught, non-blood-fed female adult *Anopheles* spp. mosquitoes captured during Human Landing Catches which have never been gravid as determined by the method of Detinova. The outcome is assessed in a sub-sample of clusters, houses, and nights on a monthly basis.Mosquito abundance—The number of adult *Anopheles* spp. captured in CDC UV Light traps.Sporozoite rate—The number of adult female *Anopheles* spp*.* captured via HLC or CDC UV light traps found to be sporozoite positive by anti-circumsporozoite protein (α-CSP) enzyme-linked immune-sorbent assay (ELISA) divided by the number of adult female *Anopheles* spp. tested in ELISA assay.Human landing/biting rate—The number of adult female *Anopheles* spp. captured via HLC divided by the number of person-nights (days) of HLC collection.Entomological inoculation rate—The human landing/biting rate (6) multiplied by the sporozoite rate (5) multiplied by 365 days per year to yield annualized EIR. It should be noted that all EIR estimates will be expressed in terms of annual rates.

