### EIR

The analysis of the entomological inoculation rate will utilize data derived from capture of adult *Anopheles* spp. mosquitoes caught via HLC or CDC light trap indoors or outdoors only and will follow similar principles to the analysis of total sporozoite-positive mosquitoes. The analysis will be based on Student’s *t*-test. For this analysis, estimates of EIR will be made independently for each cluster by calculating an estimated annual EIR within each cluster according to the following formula.$$EIR= \sum_{i=1}^{n}{30s}_{i}\left\{\begin{array}{c}\frac{\sum_{j=1}^{m}{b}_{ij}}{\sum_{j=1}^{m}{d}_{ij}};if \sum_{j=1}^{m}{d}_{ij}>0\\ 0;otherwise\end{array}\right.$$where EIR equals the number of infected bites per person night per year and *n* represents the number of months of the year. Where collections are not made during the full calendar year because the malaria transmission season is assumed to be short and infectious bites are not expected outside of the transmission season, zero will be substituted for the estimated number of infectious bites per person-day during these months as shown in the formula above. In the formula above, *b* represents the number of mosquitoes captured via HLC on a catch person-night *j* during month i*, s* represents the estimated sporozoite rate for each cluster in month *i*, *d* represents the number of person catch-days for person catch night *j* in month *i* (which will generally be equal to one), and finally, *m* represents the total number of observations (person catch-nights) of HLC conducted. EIR within each cluster will be summarized as a single annualized EIR estimate post-intervention. The cluster estimates of the EIR will be compared across arms using a Student’s *t*-test. Results will be presented as mean annualized EIR and standard deviation of annualized EIR as well as *t*-statistic and *p*-value. 95% CIs for mean parity will also be presented for each arm. Should the distribution of EIR be substantially non-normal a non-parametric test such as the Mann–Whitney *U*-test may be considered.

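### The annual EIR is defined in three ways that do not agree, and the analysis formula scores a missed in-season month as no infectious bites

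*SAP article*

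**What the plan says.** Three current sections of the SAP article define the annual EIR.

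- **Outcome list** (Timing of outcome assessments, Secondary outcomes): the landing rate is "multiplied by the sporozoite rate (5) multiplied by 365 days per year to yield annualized EIR".
- **Outcome definition** (Analysis, Secondary outcomes, item 7): "the month-specific human landing/biting rate will be multiplied (6) by the month-specific sporozoite rate (5) to yield month-specific EIRs", and then "Month-specific EIRs will be summed over the months of the year to yield the number of infectious bites expected in each year". The landing rate itself (item 6) is the HLC catch "divided by the number of person-nights (days) of HLC collection", so it is a nightly rate.
- **Analysis formula** (Analysis methods, Secondary outcomes, EIR): for each cluster, sum over the months of the year 30 × monthly sporozoite rate × (HLC catch ÷ person catch-nights). A month with no catch-nights contributes 0. The text explains the zero for sites with a short transmission season, where collections stop because no infectious bites are expected: "zero will be substituted for the estimated number of infectious bites per person-day during these months as shown in the formula above".

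The formula yields one annualized EIR per cluster. These values are compared between arms by a t-test and reported as means and standard deviations. Table 4 has a row headed "Number of months of sampling per cluster" with the values 12 (Kenya), 8 (Zambia) and 24 (Mali), and does not say whether they are per year.

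**The concern.** The three rules use different multipliers (365, none, and 30 per month) and treat unsampled months differently. The outcome definition does not deliver the unit it claims: a sum of nightly products is not a number of bites per year. This is the master plan from which three site plans are written, so sites could follow different sections and report EIRs on different scales.

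A second problem lies inside the analysis formula. The stated reason for the zero covers only months outside a short season, but the zero branch depends only on whether there were catch-nights. A collection missed during the season is then scored as if nobody received an infectious bite. Each cluster gives one value, and Table 4 lists only 8 (Kenya), 10 (Zambia) and 15 (Mali) clusters per arm, so a few such months could move the result.

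**Working it through.** The plan states no EIR value, and no sample size or power for EIR, so there is no figure to reproduce. The three rules can be compared algebraically.

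**Inputs.** Let *e* be the nightly landing rate × sporozoite rate, taken as constant, and *m* the sampled months per year. The multipliers are those given in the three sections. I assume that the outcome list averages its rates over sampled months only, which it does not say.

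**Formulas.**
- Outcome list: A = 365*e*
- Outcome definition: B = *m* × *e*
- Analysis formula: C = 30 × *m* × *e*

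Hence C/B = 30 for every *m*, A/C = 365/(30*m*) and A/B = 365/*m*.

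| Sampled months per year | A/C | C/B | A/B |
|---|---|---|---|
| 12 | 365/360 = 1.014 | 30 | 30.4 |
| 8 | 365/240 = 1.52 | 30 | 45.6 |
| 6 | 365/180 = 2.03 | 30 | 60.8 |
| 4 | 365/120 = 3.04 | 30 | 91.3 |

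**Which row applies.** Mali's 24 months cannot be per year. If the whole Table 4 row is a two-year total, Kenya has 12/2 = 6 months a year, Zambia 8/2 = 4 and Mali 24/2 = 12. If the Kenya and Zambia entries are per year, they are 12 and 8. The range therefore has to be shown.

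**Effect of scale on the test.** If every cluster value is multiplied by 30, the difference in means and its standard error both grow 30-fold. The t-statistic, the p-value and the ratio of arms do not change. The means, the standard deviations and any confidence interval on the EIR scale do. The factor 365/(30*m*) cancels in the same way only if every cluster has the same *m*.

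**Product of averages.** If the outcome list uses whole-period rates, 365 × mean landing rate × sporozoite rate matches a sum of monthly products only when the sporozoite rate is weighted by HLC catch. The plan's sporozoite rate also includes light-trap specimens, so this weighting is not assured.

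**Missed in-season month scored as zero.** At a flat rate, one missed month of *m* lowers the cluster's EIR by 1/*m*:
- 12 months: 1/12 = 8.3%
- 8 months: 1/8 = 12.5%
- 6 months: 1/6 = 16.7%

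The loss is larger if the peak month is missed. In one assumed 12-month profile the monthly products sum to 1.44 and the peak month contributes 0.45, so missing it removes 0.45/1.44 = 31%. That profile is an illustration, not trial data.

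**The case against.** The strongest reply is that the analysis section gives an explicit formula and the other two are loose prose. The outcome definition twice labels its result as bites per year, so an analyst would see that a days factor had been left out. A constant factor cannot alter the arm comparison. The zero substitution is explained by the short season, and an analyst who respects that explanation would not apply it in season. With 10 households per cluster planned each month, a whole month without catch-nights should be uncommon. Parity, not EIR, is called the main entomological outcome.

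Much of this stands. A reader might infer from a 30-fold gap that the test of the intervention on EIR is at risk; the documents do not support that, because the factor cancels. A reader might also take the 1.5-fold gap as established for Zambia. It depends on reading Table 4's 8 months as per year and on averaging over sampled months only, and the plan states neither. Nor does anything in the plan suggest that missed months will differ between arms, so a bias between arms is a possibility and not a finding.

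The reply does not remove the conflict. All three rules are current, none is said to take precedence, and the formula's zero branch as written contradicts its own rationale.

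**Conclusion.** The inconsistency is real and should be corrected. It is a defect in the definition and reporting of one secondary outcome, and the primary outcome is unaffected.

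- The outcome definition, followed literally, gives annual EIRs 30-fold below the analysis formula. This holds for any number of sampled months and affects absolute values only.
- The 365 version and the formula are within about 1.4% with 12 sampled months a year. They are 1.5-fold apart at 8 months, 2.0-fold at 6 and 3.0-fold at 4, given a constant rate and averaging over sampled months only.
- The zero branch is the part that can reach the arm comparison. It lowers an affected cluster's EIR by about 8% to 17% per missed in-season month at a flat rate (12 to 6 months). It adds noise if missed months vary between clusters, and bias if they vary between arms.

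**What to change.** Use one formula in all three sections: the sum over months of (days in month) × (monthly landing rate) × (monthly sporozoite rate). Delete the version multiplied by 365 and the sum without a days factor.

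Apply zero only to months outside a transmission season stated in advance for each site. Treat an in-season cluster-month as missing if it had no catch-nights, or if mosquitoes landed but none were tested. A month with catch-nights and no landings is an observed zero and stays one.

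State in advance a rule for missing months that does not use arm, for example the cluster's own sampled in-season months scaled to the season length. Do not fill gaps with the model predictions planned for the sporozoite and landing rates. Those are by arm, month and indoor or outdoor location, so they would build the estimated arm effect into the cluster values and shrink the variation between clusters.

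Say in Table 4 whether sampling months are per year or for the whole trial.

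The cost is wording in the master SAP and the site SAPs. No new data are needed.

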## Analysis methods

### Primary outcome

The primary unadjusted analysis will be conducted on the intention-to-treat analysis population without adjustment for any anticipated confounding variables as these are considered to be balanced due to randomization. The analysis of the primary outcome, cumulative clinical incidence of malaria, will be analyzed using a multi-level (variance components model) constructed on a generalized linear model framework with a Poisson likelihood and a log link function. Random intercepts will be included for each study cluster and study arm will be included as a fixed effect coded categorically as 0 for arm A and 1 for arm B. The analyst will be blinded to the true assignment until the allocation code is broken. The model will take the form below where *y*_*ij*_ is incidence at the individual level (*i* indexes individuals within clusters and* j* indexes clusters), *α* is the global intercept, *X*_*ij*_ is the arm assignment for individual *i* in cluster *j*, *β*_*arm*_ is the arm effect to be estimated, *u*_*j*_ are random intercepts for the cluster and *exposure*_*i*j_ is the person time at risk for individual *i* in cluster *j*, *λ*_*ij*_ refers to the *E(y*_*ij*_*|u*_*j*_*)*, and *σ* is the standard deviation of the random intercept distribution:$$\mathrm{log}E\left({y}_{ij}|{u}_{j}\right)=\alpha +{X}_{ij}^{arm}{\beta }_{arm}+{u}_{j}+\mathrm{log}({exposure}_{ij})$$where the likelihood is of the form:$${y}_{ij}\sim Pois({\lambda }_{ij})$$

And the random intercepts are assumed to follow a normal distribution:$${u}_{j}\sim N(0,{\sigma }^{2})$$

Results will be presented as the incidence rate ratio (IRR), corresponding 95% confidence interval, and *p*-value based on the *z*-statistic. The primary outcome will also be checked for the distributional assumption that the mean and variance of the outcome are similar after conditioning on cluster (e.g., are the within-cluster mean and variance similar). If variance is substantially larger, a negative binomial likelihood will be considered.

